### Study setting

The research assistants will obtain written consent (version 1.0, 30 June 2017) from the patients potentially eligible for the study. A researcher will explain the manipulation of acupuncture treatments used in traditional Chinese medicine (TCM) clinics. Subsequently, a researcher will screen whether the patient can participate in the study. If the patient fulfills the inclusion/exclusion criteria, a clinical research coordinator (CRC) specified by the scientific research department, Baoshan Hospital of Integrated Traditional Chinese Medicine and Western Medicine, Shanghai will contact an independent researcher who has the random number table; the participants will be randomly allocated into one of the three groups (group A, B, or C) at a 1:1:1 allocation ratio. All participants will receive conventional acupuncture therapy; however, the participants assigned to group A will be given additional acupuncture on the acu-point Bi’nao, while the participants assigned to group B will be given extra acupuncture on a point 1 cm backward to Bi’nao as a placebo point. Only group C participants will not receive extra acupuncture on any other acu-point.

The participants of this trial will undergo acupuncture treatments three times a week for one month. The Eye Crack Width Measurement (ECWM) and Eyelid Strength Assessment (ESA) of all the participants will be performed at the allocation time point, weekly during the treatment duration, and one month after the first therapy. The first ECWM and ESA value will be recorded as a baseline and the final values will be recorded as the end-time measurement. The follow-up visits for all participants will be scheduled at three months after the first acupuncture therapy. After the participants have completely recovered from hypophasis, the acupuncture therapy will be stopped and the final ECWM and ESA values will be recorded as an end-time measurement.

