### Intervention

#### Acupuncture treatment

Acupuncture will be performed by specialists in TCM and follow the STRICTA 2010 checklist (Table 1).

**Table 1 Tab1:** Details of acupuncture intervention (according to the Standards for Reporting Interventions in Clinical Trials of Acupuncture (STRICTA) 2010 guidelines Expansion of Item 5 from Consolidated Standards of Reporting Trials 2010 guidelines)

Acupuncture rationale	Style of acupuncture	Traditional Chinese Medicine
	Rationale for treatment	Acupuncture has been historically used to treat hypophasis in facial palsy. Additionally, it is known to be a safe treatment used in a wide range of symptoms caused by Bell’s palsy
	Extent to which treatment varied	The participants in the intervention group all receive the same manual acupuncture treatment
Details of needling	Number of needle insertions per individual per session	8–9
	Names of the insertion points (uni/bilateral)	BL2, GB14, SJ23, Shangming, LI14 (unilateral, affected side); SJ5, KI6(bilateral)
	Depth of insertion	10–30 mm (exact depth shown in Table 2)
	Response sought	De-qi
	Needle stimulation	Manual stimulation (exact details are in the text)
	Needle retention time	20 min
	Needle type	0.30 mm (diameter) × 25 mm (length) disposal needle (Huatuo Acupuncture Inc., Suzhou, China)
Treatment regimen	Number of treatment sessions	12
	Frequency and duration of treatment sessions	3 sessions per week for 4 weeks
Other components of treatment	Details of other interventions administered to the acupuncture group	No other interventions are done
	Setting and context of treatment	All participants are informed that they will receive acupuncture treatment, which can potentially reduce symptoms of hypophasis; however, the control group will have to complete the evaluations during the first week before receiving the same treatment as the acupuncture group
Practitioner background	Description of participating acupuncturists	Specialists in TCM with at least 3 years of practice in acupuncture
Control or comparator interventions	Rationale for the control or comparator in the context of the research question	Sham acu-point is used as a placebo control
	Precise description of the control or comparator	Placebo control group be given extra acupuncture on a point 1 cm backward to Bi’nao as a placebo point

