#### Follow-up

All participants will be followed up at three months after the first acupuncture therapy, including those who completely recovered from hypophasis within one month. The follow-up will be accomplished by a clinic visit or telephone survey about the progress and recurrence of hypophasis.

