### Safety issues

Adverse events (AEs) will be recorded using the standard operating procedures for monitoring and reporting all AEs, which refer to all the harmful and unintended reactions that occur during the acupuncture treatment. The symptoms, date of occurrence, disappearance, causality, and severity of the AEs will be recorded. The putative AEs of acupuncture include the following: local bleeding or hematoma; more than slight sharp pain; aggravation of symptoms; syncope; nausea; headache; peripheral nerve injury; and infection. Participants will be informed of the potential AEs in advance.

During the study period, all researchers will ensure patient safety. When SAEs occur, the researchers will immediately halt the study and promptly provide appropriate management. The PI will also report the AEs to the IRB and halt the study partially or completely until further notice. Then, the IRB will determine whether the clinical study can be continued. The trial will be stopped if the IRB speculates unacceptable risks of SAEs. The hospital provides insurance coverage for harm associated with the interventions during this trial as necessary.

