#### Statistical analysis

In this study, rather than the investigator, professionals will analyze the data using intention-to-treat and per-protocol approaches. The demographic and clinical characteristics of the participants (such as sex and age) will be processed based on descriptive analyses. The ECWM values and ESA scores will be compared as a baseline measurement. The quantitative data will be presented as average, standard deviation, median value, and range, while the qualitative data will be presented as the frequency and percentage.

For the primary and secondary outcome measurements, one-way ANOVA test will be applied to identify the differences between the of ECWM values and ESA scores among the groups. In case of abnormally distributed data, Kruskal–Wallis H test will be performed.

All AEs reported during the study will be included in the clinical report; then, the prevalence of AEs will be calculated. The percentage of participants with AEs in each group will be calculated and compared using the chi-squared or Fisher’s exact test. Statistical analyses will be performed using IBM SPSS Windows version 19.0 (IBM Co., Armonk, NY, USA). The tests were two-sided; a *P* value < 0.05 will be considered statistically significant.

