### Ethics and dissemination

The study was planned in accordance with the Helsinki Declaration and the Korean Good Clinical Practice Guidelines to protect the participants and was approved by the Medical Ethics Committee Board of Baoshan Hospital of Integrated Traditional Chinese Medicine and Western Medicine, Shanghai (201709–02). The participants will be informed of the potential benefits, risks, alternatives, and responsibilities of the study by the researchers during the consent process. They will be fully aware that they are free to withdraw from the study at any time. Any AEs (described as unfavorable or unintended signs, symptoms, or diseases occurring after treatment) related to acupuncture treatment will be observed and reported by patients and practitioners during each patient visit. In addition, all vital signs and AEs will be measured and recorded during each visit. The findings will be disseminated in peer-reviewed journals and conference presentations.

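### The percentage of participants with adverse events cannot separate safer needling from less needling, because sessions stop at recovery

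*Protocol article*

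**What the plan says.** All references are to the protocol article.

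- **Exposure.** Under Acupuncture treatment, Table 1 plans 12 sessions, given as "3 sessions per week for 4 weeks". Study setting adds a stopping rule: "After the participants have completely recovered from hypophasis, the acupuncture therapy will be stopped". The final eyelid measurements are then taken as the end-time values.
- **AE definition.** Safety issues describes AEs as "harmful and unintended reactions that occur during the acupuncture treatment".
- **AE collection.** Ethics and dissemination says that AEs related to acupuncture "will be observed and reported by patients and practitioners during each patient visit", and continues: "In addition, all vital signs and AEs will be measured and recorded during each visit".
- **Later contact.** Follow-up says: "All participants will be followed up at three months after the first acupuncture therapy, including those who completely recovered from hypophasis within one month". This contact is a clinic visit or a telephone survey. Its stated subject is the course and return of the eyelid problem, and AEs are not named.
- **Analysis.** Statistical analysis says "All AEs reported during the study will be included in the clinical report; then, the prevalence of AEs will be calculated". The comparison between arms follows: "The percentage of participants with AEs in each group will be calculated and compared using the chi-squared" or Fisher's exact test, with no denominator of sessions or time.

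**The concern.** A participant who recovers halfway through receives about half the planned needling, and so has about half the opportunity for a needle reaction. If one arm recovers faster, its participants have fewer sessions on average. Its percentage with any AE then falls even when each session carries the same risk. If each session carries somewhat more risk, the two effects can cancel and the arms look alike.

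This matters because safety is one of the article's stated interests: the abstract's Discussion speaks of assessing both safety and efficiency. Group A also receives one more needle per session than Group C. The eight basic insertions are four unilateral points and two bilateral ones, and Bi'nao makes nine. A reader of the AE table will want to know whether the added point does harm, and the crude percentage does not answer that on its own.

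A second, smaller question is whether early recoverers are asked about AEs as often as the others. Study setting schedules the eyelid assessments for all participants weekly during treatment and at one month. It also makes the value at recovery the end-time measurement. It does not make clear whether someone whose therapy has stopped keeps the remaining visits.

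**Working it through.** **The plan's own figures.** The article states no AE rate, recovery rate or power for AEs, so there is no AE figure to reproduce. The figures used from it are 12 planned sessions, 33 participants per group, and 9 needles per session in Groups A and B against 8 in Group C.

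**Model (assumed).** Let q be the AE risk per session, constant and independent across sessions. Over k sessions, P(any AE) = 1 − (1 − q)^k. The slower arm has all 12 sessions. In the faster arm a share f stops after s sessions:

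P(faster) = f·[1 − (1 − q)^s] + (1 − f)·[1 − (1 − q)^12]

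**Worked case.** Take q = 2%, f = 50%, s = 6.

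- Slower arm: 1 − 0.98^12 = 21.5%.
- Six sessions only: 1 − 0.98^6 = 11.4%.
- Faster arm: 0.5 × 11.4% + 0.5 × 21.5% = 16.5%, with a mean of 0.5 × 6 + 0.5 × 12 = 9 sessions.
- Risk ratio: about 0.77, although the per-session risk is identical.

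**Range.** Each cell gives the percentage with any AE in the faster arm, with the risk ratio against the slower arm in brackets.

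| f, s | q = 1% (slower arm 11.4%) | q = 2% (slower arm 21.5%) | q = 5% (slower arm 46.0%) |
|---|---|---|---|
| 25%, 9 | 10.7% (0.94) | 20.3% (0.94) | 43.7% (0.95) |
| 25%, 6 | 10.0% (0.88) | 19.0% (0.88) | 41.1% (0.89) |
| 50%, 9 | 10.0% (0.88) | 19.1% (0.89) | 41.5% (0.90) |
| 50%, 6 | 8.6% (0.76) | 16.5% (0.77) | 36.2% (0.79) |
| 75%, 9 | 9.3% (0.82) | 17.9% (0.83) | 39.2% (0.85) |
| 75%, 6 | 7.2% (0.64) | 13.9% (0.65) | 31.4% (0.68) |

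The ratio runs from 0.64 to 0.95. It is 1.0 when f is zero or when both arms stop alike. Under this model AEs per session give a ratio of 1.0 in every cell.

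**Early recovery in both arms.** With q = 3%, 40% of one arm and 10% of the other stopping after 6 sessions, the shares are 25.1% and 29.2%. The gap is 4.2 points before rounding, or about 1.4 of 33 participants.

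**Masking.** Give the faster arm 1.33 times the per-session risk (4/3 × 2% = 2.67%), with half of it stopping after 6 sessions. Then P(faster) = 0.5 × [1 − 0.9733^6] + 0.5 × [1 − 0.9733^12] = 21.3%, against 21.5% in the slower arm. A real one-third increase per session disappears from the percentage.

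**Extra needle, A against C.** If risk scales with needles (9/8) and q = 2% in Group C, Group A shows 18.3% (f = 50%, s = 6), 21.1% (25%, 6), 21.2% (50%, 9) or 22.6% (25%, 9), against 21.5% in Group C. The two influences pull in opposite directions. Groups A and B have equal needle counts, so the exposure effect is cleanest there.

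**Significance.** At 33 per arm, the gaps in the table would give P < 0.05 with probability of about 3% to 23%.

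**The case against.** **The percentage is legitimate.** Stopping at recovery is part of the regimen in every arm. Fewer sessions really do produce fewer needle reactions, and sessions received is a consequence of randomised treatment, not a confounder. This stands. A reader might infer that the safety comparison is confounded or that a lower percentage would be spurious. The article does not support that: the percentage answers a proper question about the treatment policy and is never presented as a per-session risk.

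**Loss of contact is not shown.** A reader might also infer that early recoverers go unobserved until three months. Study setting schedules weekly and one-month assessments for all participants. The three-month contact covers everyone, and all AEs reported during the study are counted. The visit schedule figure and the AE operating procedures are not available to check. Many of the listed reactions, such as sharp pain or fainting, would be expected around the session itself, so little may be missed once needling stops. What remains is an ambiguity about the schedule, not a demonstrated gap.

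**The numbers are assumed.** This is true. No AE or recovery rate is given, and the effect vanishes if early recovery is rare or balanced. The gaps amount to a few participants per arm at most and would seldom reach significance.

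**Exposure tables belong in the analysis plan, and the per-session rate has its own assumption.** The absence of such a table is not itself a fault. The point rests on what the article does fix: outcome-dependent stopping together with a participant percentage as the stated comparison. The warning about the rate also stands. If reactions cluster in the first sessions, the faster arm has fewer low-risk later sessions in its denominator and would look worse than it is. The rate should therefore supplement the percentage, not replace it.

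**Conclusion.** The point holds in limited form. Needling exposure depends on the efficacy outcome, and AE enquiry may do so too. The planned percentage therefore describes the policy but cannot show whether the needling itself is more or less safe. It could hide a higher per-session risk in an arm that recovers faster.

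The size cannot be known from the article. The 0.64–0.95 range rests on constant and equal per-session risk, all 12 sessions in the slower arm, and 25–75% of the faster arm stopping after 6–9 sessions. The harm is to how the estimate is read and to the chance of missing a real difference, more than to false significance. Two stronger readings, an invalid AE comparison and early recoverers lost to AE observation, go beyond the text. This is a cheap improvement, not a defect that undermines the trial.

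**What to change.** 1. State that AEs are asked about on the same schedule for every randomised participant (weekly, at one month and at the three-month contact), whether or not therapy has stopped. A telephone enquiry is enough. Say explicitly in Study setting whether early recoverers keep the weekly and one-month assessments.
2. Keep the percentage of participants with AEs and its test as planned.
3. Beside it, tabulate sessions received and AEs per session by arm as a supplementary analysis, with a note that the per-session rate assumes constant risk over sessions.

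The cost is a few short calls per early recoverer and one extra table. Treatment and the stopping rule are untouched.

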**Discussion:**

This is the first study assessing the safety and efficiency of Bi’nao in treating the hypophasis of patients with Bell’s palsy that might support the application of this acupuncture therapy. However, evaluating hypophasis is challenging, and, thus, ECWM and ESA were applied to measure the eyelid movement.

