## Methods/design

### Objective

The present study assessed the augmenting effect of acupuncture therapy on the acu-point Bi’nao for hypophasis through eye crack width and eyelid strength compared to a sham acu-point and no acupuncture treatment on Bi’nao.

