### Statistical methods

#### Sample size calculation

The enumeration data of parallel-controlled trial (1:1:1) are analyzed statistically using two-sided superiority test, where α = 0.05, power = 90%. The formula used for the calculation was as follows:$$ n\kern0.5em =\kern0.5em \frac{{\left({Z}_{1-a}+{Z}_{1-\upbeta}\right)}^2\kern0.5em \times \left({\sigma}_1^2+{\sigma}_2^2\right)}{\delta^2} $$

The change in the standard deviation of ECWM score before and after the treatment in the control group was presumed as 1 point and that in the treatment group as 3 points. This will be considered clinically significant if the change in the ECWM score before and after the treatment in the treatment group is 2 points higher than that in the control group, and the sample size was estimated as follows:$$ n\kern0.5em =\kern0.5em \frac{{\left({Z}_{1-a}+{Z}_{1-\upbeta}\right)}^2\kern0.5em \times \left({\sigma}_1^2+{\sigma}_2^2\right)}{\delta^2}\kern0.5em =\kern0.5em \frac{{\left(1.96+1.28\right)}^2\kern0.5em \times \left({1}^2+{3}^2\right)}{2^2}\kern0.5em =\kern0.5em 26 $$

Thus, a minimum of 27 patients was estimated in each group. The dropout rate is considered to be 20%; therefore, at least 33 patients should be enrolled in each group. Hence, a total of 99 patients are required to conduct this study.

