## Discussion

The present study evaluated the efficacy of acupuncture therapy on the acupoint Bi’nao for hypophasis in patients with Bell’s palsy based on the previous studies and our clinical experience. When planning a manual acupuncture study, the duration of treatment, treatment points, and frequency of stimulation should be considered as these can affect the outcomes of acupuncture. However, in a RCT, only one variable could be tested. Thus, we established this regimented acupuncture protocol that has been discussed and optimized at the Baoshan Hospital of Integrated Traditional Chinese Medicine and Western Medicine, Shanghai.

In addition, the function of “De qi” will be considered in the trial; it is based on subjective reporting of the patient (soreness, numbness, fullness, radiating sensation) and is regarded as a sign of efficacy according to TCM. A majority of the contemporary acupuncturists still seek “De qi,” rendering it as fundamental to efficacy. The placebo effect produced by sham acupuncture was considered to influence the disease lightly, although needle pricking might induce non-specific physiological reactions. The sensation of “De qi” can be accurately described by sense felt by either the practitioner or patient, and reliable scales such as the Massachusetts General Hospital Acupuncture Sensation Scale (MASS) have already been applied in clinics measuring the intensity of “De qi” sensation [24–26].

The assessment of hypophasis is rather challenging due to the lack of a widely recognized method or scale. The House-Brackmann scale and Sunnybrook Grading System are suitable for the overall assessment of Bell’s palsy, but are not applicable to individual symptoms such as hypophasis. Thus, we created the ECWM and ESA to evaluate eyelid movement according to some neurological function classification. Although this was an innovative approach, it was also a limitation of this study.

The results showed that the acupuncture treatment on the acu-point Bi’nao is a safe and effective method for improving hypophasis. Furthermore, the study provided evidence to support the application of acupuncture therapy in the management of Bell’s palsy and its sequelae in the future.

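### The article claims to assess safety and already concludes that Bi’nao is safe, but its only inferential adverse-event analysis is a P<0.05 difference test at about 33 per arm, and a non-significant result there would not support that claim

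*Protocol article*

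**What the plan says.** Three places in the article bear on safety as a claim.

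- Abstract, Discussion: "This is the first study assessing the safety and efficiency of Bi’nao in treating the hypophasis of patients with Bell’s palsy".
- Main Discussion, last paragraph: the treatment "is a safe and effective method for improving hypophasis", worded as a result, although Trial status says that recruitment is still under way.
- Objective: "The present study assessed the augmenting effect of acupuncture therapy on the acu-point Bi’nao for hypophasis through eye crack width and eyelid strength". Safety is not named here.

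The AE analysis is in Statistical analysis. It has a descriptive part, "All AEs reported during the study will be included in the clinical report; then, the prevalence of AEs will be calculated", and an inferential part, "The percentage of participants with AEs in each group will be calculated and compared using the chi-squared or Fisher’s exact test". The general rule for tests is "The tests were two-sided; a *P* value < 0.05 will be considered statistically significant". Safety issues adds that the timing, causality and severity of AEs are recorded, and sets out what happens after a serious event.

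Sample size calculation works only from the change in eye crack width and arrives at "at least 33 patients should be enrolled in each group". It uses no AE rate.

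**The concern.** The claim and the analysis do not match. A chi-squared or Fisher test asks whether the data contradict equal AE risks. In a small trial with uncommon events it will often fail to do so even when the risks differ materially. Failure to reject therefore says little about safety, and nothing about how large an excess remains possible.

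The comparison also names no contrast. Groups A and B each receive one extra needle in the upper arm and Group C does not. The burden of adding the Bi’nao needle therefore shows in A versus C, while A versus B isolates what is specific to the point. One comparison of three percentages estimates neither.

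At stake is the safety sentence in the eventual report. A result of no significant difference could be set beside a Discussion that already uses the word *safe*, with no figure for the excess risk that the data leave open.

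**Working it through.** **1. The plan's own figure.** Inputs from Sample size calculation: z-values 1.96 and 1.28, standard deviations 1 and 3, difference 2.

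n = (1.96 + 1.28)² × (1² + 3²) / 2² = 10.498 × 10 / 4 = 26.24, rounded up to 27. With 20% dropout, 26.24 / 0.8 = 32.8, which gives 33. (Starting from 27, 27 / 0.8 = 33.75 would give 34; the difference does not matter here.) The stated size reproduces, and no AE quantity enters it.

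**2. How often the stated test misses a doubled AE risk.** The article gives no AE rate, so the control risk p is assumed over a range and the comparison risk is 2p. For n per arm, every pair of counts (a, b) is enumerated:

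miss rate = 1 − Σ Bin(a; n, p) × Bin(b; n, 2p) × I[two-sided P < 0.05]

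The P value is from Fisher's exact test or from the uncorrected chi-squared test.

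| Assumed risks | n = 33: Fisher | n = 33: chi-squared | n = 27: Fisher | n = 27: chi-squared |
|---|---|---|---|---|
| 5% vs 10% | 97% | 88% | 99% | 91% |
| 10% vs 20% | 88% | 79% | 92% | 81% |
| 15% vs 30% | 79% | 68% | 84% | 72% |
| 20% vs 40% | 68% | 56% | 74% | 62% |
| 25% vs 50% | 52% | 41% | 63% | 52% |
| 30% vs 60% | 35% | 26% | 52% | 41% |
| 40% vs 80% | 10% | 6% | 20% | 13% |

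At 33 per arm the miss rate passes below one half between a 20% and a 25% control risk for chi-squared, and just above 25% for Fisher.

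**3. Three groups at once.** By simulation of the 2-degree-of-freedom chi-squared test at 33 per arm (40,000 runs), with A and B at 20% and C at 10%, power is 18%, so about 82% are missed. With only A doubled from 10%, power is 21%, the same as for the two-arm chi-squared test. The extra degree of freedom costs almost nothing.

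**4. What an interval would add.** As an illustration, take 7/33 participants with AEs in A and 3/33 in C.

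- Difference: 21.2% − 9.1% = 12.1 percentage points. Fisher P = 0.30.
- Wilson limits: 10.7% to 37.8% for 7/33, and 3.1% to 23.6% for 3/33.
- Newcombe lower limit: 0.121 − √[(0.212 − 0.107)² + (0.236 − 0.091)²] = 0.121 − 0.179 = −0.058.
- Newcombe upper limit: 0.121 + √[(0.378 − 0.212)² + (0.091 − 0.031)²] = 0.121 + 0.176 = 0.297.

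The result is non-significant, yet compatible with up to about 30 extra affected participants per 100. Even with no AE at all in 33, the exact two-sided 95% upper limit for the risk is 1 − 0.025^(1/33) = 10.6%.

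**The case against.** The strongest reply is that the defect is inferred. A reader might conclude that the trial will take P>0.05 as proof of safety, but no sentence says so: the article states only that percentages are calculated and compared, and its formal objective names efficacy alone. This stands. The point is that the planned test could not carry the safety wording, not that the article states a faulty decision rule.

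A reader might also infer that the test is the whole safety analysis. It is not. All AEs are to be reported, prevalence and per-group percentages are to be calculated, and causality and severity are recorded. None of this, however, bounds the excess risk.

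A third tempting reading is that the test would miss a doubling whatever the AE rate. The article does not support that. Every arm receives repeated needling and local bleeding is on the AE list, so a control risk of 30% or more cannot be ruled out, and there a doubling would be found more often than not at 33 per arm.

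Finally, low power for AEs is usual in a trial sized for efficacy, the tests are standard, and interval methods are often left to an analysis plan that is not shown. That is fair, and the test itself is no error. What remains is that the article makes a safety claim and states an analysis that cannot support it. The *safe* sentence in the Discussion, written before the data are complete, is a fault of wording that the test did not cause but that has to be corrected with it.

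**Conclusion.** The point holds in limited form. The abstract claims an assessment of safety and the Discussion already states safety as a finding. The only inferential support planned is a difference test on about 33 participants per arm, and a non-significant result from it would not justify the word *safe*.

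The size depends on an AE rate that the article does not give. For control risks up to about 20–25% the test misses a doubling more often than not; from about 30% upward, at 33 per arm, it does not. The logical point, that absence of significance is not evidence of safety, does not depend on the rate. The efficacy analysis, the sample size and the conduct of the trial are unaffected. This is an inexpensive improvement worth making.

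**What to change.** **Statistical analysis.** For the percentage of participants with any AE, report the differences A minus C (the added needle) and A minus B (specific to the point), each with a 95% Newcombe or exact confidence interval, and an exact 95% interval for Group A. Add that a non-significant AE comparison will not be read as evidence of safety and that any safety statement will quote the upper confidence limit. The chi-squared or Fisher P value may stay as a supplement.

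**Abstract and Discussion.** Describe the aim as describing the tolerability of Bi’nao, and remove the sentence that states safety as a result before the data exist.

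**Cost.** A few lines of text and a short analysis of data already being collected. No more patients and no new assessments are needed. The downside is a more modest safety claim.
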